### Randomization

An independent researcher will generate random number sequences using random allocation software with a 1:1 ratio. We will use random sequence blocks (blocks between 6 and 8), stratified by birth order (first child/ no first child) and paternal participation (yes/no). An independent researcher will allocate each consenting participant to either the control or the intervention group. Given the nature and design of the study, blinding after randomization is not possible. Participants will receive the outcome of randomization by e-mail. Please refer to Fig. 3 for an overview of participant's flow through the study.

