#### Support sessions

Parents will be visited at home during weeks 34–36 of the pregnancy. The primary aim of this home visit is to discuss the provided information (booklet and video) and to answer any questions about the materials the parents might have. The secondary aim is to explain that the provided information is not meant to be prescriptive; rather, we aim to provide parents with a set of tools (the practical examples) that they can choose from. By means of provided materials, we ask participants to start discovering which tools fit best with their and their infant’s preferences and needs.

Four weeks after the birth of their child, parents will be contacted by telephone. During this call, we will ask the parents how they and their child are doing, and whether they are experiencing any problems in implementing the information from the booklet and the video in their daily lives. Also, parents are given the opportunity to ask questions with regard to their infant’s feeding, crying, sleeping, and contact-seeking behavior. They can also ask questions with regard to their own well-being (i.e., experienced stress or feelings of anxiety). Both the home visit as well as the telephone call will be performed by the corresponding author, who has a background in clinical psychology and infant development.

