### Assessments and outcomes

We will measure at baseline (26–34 weeks of pregnancy, t0); 34–36 weeks of pregnancy (t1); 2 weeks after birth (t2); 6 weeks after birth (t3); and 10 weeks after birth (t4). All assessments will take place online, except for the completion of the infant behavior diary (t3; Fig. 2).

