### Data management

We will keep one file in which research identifiers are linked to participant’s names and (e-mail) addresses. This file will be encrypted and password protected and only be available to the main researchers. All on- and offline data will be safely stored at the university using research identifier only.

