### Dissemination policy

MM and RB will process the data, and both positive and negative findings will be disclosed, unreservedly. Results will be submitted for publication to peer-reviewed scientific journals. The participating parents as well as the participating midwifery centers will receive updates on the study’s progress. At the end of the project, results and conclusions will be presented to all those involved.

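### The plan rules out blinding without qualification, although data entry and analysis could be masked with arrangements it already has

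*Protocol article*

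**What the plan says.** The Randomization section of the protocol article makes one statement on masking: "Given the nature and design of the study, blinding after randomization is not possible". It names no role. The next sentence tells the reader that "Participants will receive the outcome of randomization by e-mail". The same section gives both the sequence and the allocation to someone outside the team: "An independent researcher will generate random number sequences using random allocation software with a 1:1 ratio".

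Four other sections bear on who could be masked:

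- Support sessions: "Both the home visit as well as the telephone call will be performed by the corresponding author".
- Dissemination policy: two team members, given by initials, "will process the data, and both positive and negative findings will be disclosed, unreservedly". No masking is mentioned.
- Data management: "All on- and offline data will be safely stored at the university using research identifier only". A separate encrypted file links identifiers to names and addresses and is open to the main researchers only.
- Assessments and outcomes: "All assessments will take place online, except for the completion of the infant behavior diary". The diary is therefore the one measure that does not arrive as an online record.

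**The concern.** Blinding is not one property of a trial. Participants, providers, those who enter or code data, and analysts can each be masked or not. The reason the plan gives settles the matter for the first two only. Parents either receive a booklet, a video, a visit and a call, or they do not, and the provider knows whom she or he has visited. Nothing in that prevents a data set from being entered and modelled with the arms labelled A and B.

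As worded, the sentence covers every role, and no other section provides for masked data handling. A team that follows it would have no reason to mask even where that is easy. In a trial whose parents necessarily know their arm, the analysis is one of the few steps that can still be protected. At stake is whether choices left open in the analysis are made by someone who can see which way each choice moves the result.

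**Working it through.** The concern is about conduct and disputes no figure, so most of the check sets sections side by side.

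**Step 1. Which roles does the stated reason cover?**

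- Parents: covered. They learn their arm by e-mail (Randomization).
- Intervention provider: covered. One author makes all visits and calls (Support sessions).
- Whoever enters the diary data: not covered. The task needs an identifier, not the arm.
- Whoever fits the models: not covered. A two-level group variable can carry neutral labels.

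**Step 2. Would the plan's own arrangements permit masking?**

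- Data are held by identifier, online and offline (Data management), so a file without names exists by design.
- An independent researcher allocates (Randomization) and is the natural holder of the arm key.
- Two people process the data (Dissemination policy) and one person delivers the intervention (Support sessions). At most one of the two processors is the provider, so at least one is not.
- One obstacle: the linking file is open to the main researchers, and anyone who knows whom they visited could work back from name to arm. Access would need to be restricted for the person doing the masked work.
- A second obstacle: the items in Intervention uptake and the video viewing logs concern materials that the control group receives only after the last assessment (Waitlist control group and care-as-usual). In the analysis file they would reveal the arm.

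Both obstacles are matters of file handling.

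**Step 3. Where could knowledge of the arm influence a result?**

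- Statistical analysis: both intention-to-treat and completers-only analyses are planned.
- Primary outcome (under Statistical analysis): effect sizes are calculated at both 6 weeks (t3) and 10 weeks (t4).
- Secondary outcomes (under Statistical analysis): control variables are named as broad classes (demographics, attachment style, delivery and birth data). That paragraph does not say whether it also governs the primary model.
- Infant well-being and health: parents flag whether the diary period was typical, and the article does not say how the flag is used.
- Diary entry: symbols in 5-minute slots have to be turned into data. The scope for influence is small, because the parents have already chosen the symbol from preset categories.
- Scoring of the primary outcome: no scope. It is completed online and is a sum of item scores (Primary outcome, under Assessments and outcomes).

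**Step 4. Size.** The document gives nothing from which a bias could be computed. The sample size fixes only how sensitive the test would be to a given shift.

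- The plan's figure: d = 0.50, 80% power, alpha 0.05 (two-sided assumed). The normal approximation gives n = 2 × (1.960 + 0.842)² / 0.50² = 62.8, so 63 per arm. The t-test gives 63.8, so 64 per arm with 80.1% power. The stated 64 per arm and 128 in total are reproduced.
- Illustration only: suppose there is no true effect and unmasked handling shifts one arm by b standard deviations. The noncentrality is b × √(64/2) = 5.66 b. The two-sided 5% test then rejects with probability 5.1% (b = 0.02), 5.9% (b = 0.05), 8.7% (b = 0.10), 13.4% (b = 0.15) and 20.2% (b = 0.20).

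Every value of b is an assumption. Nothing in the document indicates which value applies, or that b differs from zero.

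**The case against.** The strongest reply is that the sentence is being read too literally. It stands between the allocation step and the e-mail to participants, its reason fits participants and provider, and it mentions neither data entry nor analysis. Masked analysis is also commonly described in a full protocol or analysis plan, and neither is shown. Part of this stands: the authors may have meant only parents and provider, and mere silence on masked analysis would be no finding. But the article is not silent. It makes a positive and unqualified statement, and if the narrower meaning was intended, the wording should say so.

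A second reply is that loosely fixed analysis choices are best cured by specifying them in advance. That is right. Coded labels are an additional safeguard and do not replace specification.

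A reader might also infer more than the document supports:

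- *That staff would decide ambiguous diary slots, such as fussy against content, with the arm in view.* Infant well-being and health says that parents make these ratings with preset symbols. No section gives staff slots to interpret, or says whether those who enter the diary know the arm. Identifier-only storage points, if anything, the other way.
- *That the diary is a more objective measure worth special protection.* It is rated by the same unblinded parents as the other outcomes.
- *That bias is shown.* Only an avoidable risk is shown.
- *That masking is free.* The document does not say so, and access to the linking file and the uptake data would have to be separated.

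**Conclusion.** The point holds in limited form. The unqualified statement is wrong for data entry and analysis, where the stated reason does not apply and the plan's own arrangements make masking feasible. Followed literally, it leaves an avoidable risk of bias. That risk lies mainly in analysis choices: the two analysis sets, the two time points, the broadly named covariates and the use of the flag for a typical period. It lies to a minor degree in transcription of the diary.

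The risk cannot be quantified from the document, and the rejection rates above show only how sensitive the test is to assumed shifts. Scoring of the primary outcome is not affected. The dominant source of bias, reporting by parents who know their arm, diary ratings included, would not be removed.

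The conclusion rests on two assumptions: that no masking is provided in a document not shown, and that the processor who does not deliver the intervention can work without access to the linking file. This is a cheap improvement, not a flaw that undermines the trial.

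**What to change.** Limit the sentence in the Randomization section to participants and the intervention provider. Then add, in substance:

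- Diary data entry and the primary and secondary analyses are done under coded arm labels by a team member who does not deliver the intervention.
- The independent researcher holds the allocation key until the models have been run.
- Until then, the uptake items and video logs are kept in a separate file, and the person doing the masked work has no access to the file linking identifiers to names.

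The cost is minor file handling and restricted access to the linking file. The sample size stays at 128. The change can still be effective: Trial status reports that nine of 59 consented participants had completed the study, so 59 − 9 = 50 of those already enrolled had not, and recruitment was continuing. If masking is not adopted for either step, the plan should give a reason specific to that step.

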### Intervention

Parents will receive access to the psycho-education materials (booklet and video) directly after randomisation, which is between the 26th and the 34th weeks of pregnancy (depending on when the parents apply for participation). The intervention further consists of two support sessions: one home visit between 34 and 36 weeks of pregnancy and one telephone call 4 weeks after birth.

#### Psycho-educational booklet and video

In general, the intervention conveys the importance of responding sensitively to the needs of the infant. The psycho-educational booklet developed by Hiscock et al. [27] was used as a starting point. We developed and extended the intervention further based on recent empirical research and together with a number of different experts on attachment (researchers), breastfeeding (lactation consultants), and pre and postnatal care for both mother and child (midwives). Our booklet consists of four chapters about: (1) sensitive responding and making contact with the baby, (2) crying, (3) feeding, and (4) sleeping. The first chapter includes information about contact-seeking behavior of the baby and how to interpret infant’s signals of distress and respond to these adequately (e.g., [9]). The chapter also includes information explaining the needs of the infant (such as the need for closeness, skin-to-skin contact, and sensitive care), followed by a discussion about the parent’s own needs and how to attend to these. Then, the booklet continues with a chapter about crying. The normal crying curve is addressed, and different tools are provided on how to sooth a baby. Also, potential causes of excessive crying are discussed. The third chapter about feeding includes information about hunger signals that the baby might convey. Information is given on breastfeeding, and its positive effects for both mother and child. Practical information about the use of formula milk is also provided. The fourth and final chapter on sleeping provides information on average sleeping patterns and sleep signals that a tired baby might convey. Moreover, the importance of room-sharing during the first 6 months will be discussed and suggestions on when and how to support the infant in learning to sleep alone in a separate room are given. It is also important to note here that sensitive care is put central in our intervention, and that, for example, “crying it out” and “camping it out” techniques [32], in which parents are instructed to let infants cry for a specified amount of time, are not included in our intervention. The booklets ends with a section about common baby myths, such as “Keeping the baby awake all day, will make the baby sleep better during the night” or “When I pick up my baby every time, I will spoil the baby.” The booklet consists of written text and pictures. Most importantly, the booklet provides many examples on how to use the information in daily life. In the booklet, it is explained that the provided information is not meant to be prescriptive; rather, it encourages parents to distil those elements that are most helpful for them in their specific situation (while keeping the principles of sensitive care in their mind). This way, parents can start discovering which tools fit best with their and their infant’s preferences and needs.

At the same time as the booklet, participants receive access to an online video. This video is developed by psychologists who are experts in promoting the mental health of babies and their parents by translating academic knowledge into easily accessible interventions (Stichting Babywerk, The Netherlands). The video serves as an illustration of the topics which are described in the booklet and shows practical examples. It is a story format in which the experiences of (upcoming) parents are shown. An expert on infant development comments on each of the fragments. Also, after each fragment, participants are confronted with a thought-provoking question about what they just have seen. The aim of these questions is to stimulate participants to think about the information in relation to their lives. For example, in the story, the upcoming mother is worried that she will be unable to put her mobile phone away when her baby is awake. At this point, the participant will be asked what their thoughts are about this issue. Next, the expert explains why being able to recognize and respond to the infant’s signals is important. After the explanation, the video shows how to notice and respond to an infant seeking eye contact. Watching the video and responding to the questions takes about 15–20 min. The parents are encouraged to put this advice into practice after the birth of their child.

#### Support sessions

Parents will be visited at home during weeks 34–36 of the pregnancy. The primary aim of this home visit is to discuss the provided information (booklet and video) and to answer any questions about the materials the parents might have. The secondary aim is to explain that the provided information is not meant to be prescriptive; rather, we aim to provide parents with a set of tools (the practical examples) that they can choose from. By means of provided materials, we ask participants to start discovering which tools fit best with their and their infant’s preferences and needs.

Four weeks after the birth of their child, parents will be contacted by telephone. During this call, we will ask the parents how they and their child are doing, and whether they are experiencing any problems in implementing the information from the booklet and the video in their daily lives. Also, parents are given the opportunity to ask questions with regard to their infant’s feeding, crying, sleeping, and contact-seeking behavior. They can also ask questions with regard to their own well-being (i.e., experienced stress or feelings of anxiety). Both the home visit as well as the telephone call will be performed by the corresponding author, who has a background in clinical psychology and infant development.

### Waitlist control group and care-as-usual

Parents in the waitlist control group will receive the same materials as the parents in the intervention group after the last assessment (10 weeks after birth). The information can still be of use for them at that time. Both groups, the intervention and control group, will have access to care-as-usual during the postpartum period. In the Netherlands, this consists of regular consults with a specialized nurse at home (2 weeks after birth) or at the well-baby clinic (at 4, 8, and 12 weeks after birth) during which the health of the infant is checked upon and the infant’s growth is followed.

### Assessments and outcomes

We will measure at baseline (26–34 weeks of pregnancy, t0); 34–36 weeks of pregnancy (t1); 2 weeks after birth (t2); 6 weeks after birth (t3); and 10 weeks after birth (t4). All assessments will take place online, except for the completion of the infant behavior diary (t3; Fig. 2).

#### Baseline variables

At baseline (t0), we assess the demographic characteristics of the parents (date of birth; marital status, income, educational level, and working hours).

Furthermore, to control for possible insecure attachment styles of the parents (which can have an impact on their caregiving quality (e.g., [22]), we will measure attachment styles of the parents using the short form of the Experiences in Close Relationships Questionnaire (ECR-short form; [15, 34]^1^). The 12 items of this instrument are derived from the avoidance and anxious attachment subscales of the ECR-R (six items of each subscale; [10]). Response options vary from 1 (strongly disagree) to 7 (strongly agree). The avoidance subscale measures the need to stay independent from others and to avoid intimacy ([34], see also [7]). The anxiety subscale is concerned with the degree to which the subject worries about rejection and abandonment ([7, 34]). Following recoding of items 15, 25, 27, 29, and 31; for each subscale (anxiety and avoidance) an average score of between 1 and 7 can be computed. Higher scores reflect more attachment anxiety and avoidance. The ECR-short form showed good psychometric properties in different samples: Lafontaine et al. [34] reported Cronbach’s alpha’s of .78 to .87 for the anxiety subscale and .74 to .83 for the avoidance subscale.

#### Primary outcome

The primary outcome is maternal parenting stress (assessed at t0; t1; t3; and t4) and is measured with 10 items of the Dutch version of the Parenting Stress Index (PSI; [1, 18]). The complete version of this instrument consists of 123 items. A shortened version of 25 items is available [19]. However, since the PSI has been originally developed for parents of children up to 14 years [18], our aim was to select the 10 items that are most relevant for parents of a newborn child. Following the procedure of Missler et al., [39], we selected those items that, in our view, best captured their experience. One item was added because it was considered to be central to the parenting stress construct (at least for parents with very young children): “The responsibility I have for my children weighs on me” Missler et al., [39]. An example item is: “I feel restricted by my responsibilities as a parent.” For the administration before birth (t0 and t1), the items were slightly rephrased to capture possible stress-raising expectations of parenthood: “I expect to feel restricted by my responsibilities as a parent.” Response options vary from 1 (totally disagree) to 6 (totally agree). A total score can be derived by summing the individual item scores. This total score (including the added item) ranges from 11 (no stress) to 66 (very high stress).

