**Methods/design:**

In this randomized controlled trial, 128 pregnant women and their partners will be recruited through midwifery practices and general media. Women with a complicated pregnancy, current psychopathology, insufficient Dutch language proficiency and without Internet access will be excluded. Parents will be randomized to either the intervention or a waitlist control group. The intervention consists of a booklet and video (offered prenatally), a home visit at 34–36 weeks of pregnancy and a telephone call 4 weeks after birth. Information and practical tools are provided on (1) sensitive responding and making contact with the baby, (2) crying, (3) feeding, and (4) sleeping. Assessments will take place at baseline (26–34 weeks of pregnancy), during the home visit (34–36 weeks of pregnancy), and 2, 6, and 10 weeks after birth. The control group will be offered the intervention after the end of the study. The primary outcome is maternal parenting stress. Secondary outcomes are: paternal parenting stress, parental well-being, quality of caregiving, and infant well-being and health.

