### Objectives

The primary objective of this study is to determine the postpartum effect of the intervention on maternal parenting stress. Secondary outcomes are: paternal parenting stress, parental distress in general (anxiety and depression) and parental well-being (satisfaction with the parental role, and self-efficacy in caring for the infant); quality of caregiving (bonding, breastfeeding, and co-sleeping); and infant well-being and health (crying, feeding, sleeping, well-being, and health).

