**Fig. 2 Fig2:**
[figure not shown]
Standard Protocol Items: Recommendations for Interventional Trials (SPIRIT) Figure with trial design and outcome assessments. After screening for eligibility, participants are asked to sign an informed consent form and to complete the baseline questionnaire. Then, participants are randomized in either the intervention or the control group. The intervention starts with a home visit (at t1) and a postnatal telephone call (4 weeks after birth). Measurements take place at 26–34 weeks of pregnancy (baseline; t0); 34–36 weeks of pregnancy (t1); 2 weeks after birth (t2; delivery characteristics); 6 weeks after birth (t3); and 10 weeks after birth (t4)

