#### Primary outcome

We will compare the parenting stress scores between the two groups using a mixed multilevel model. This way, we can account for the nested structure of the data (mothers and fathers that belong to the same couple). Including both mothers and fathers in one analysis, will positively affect the power of the analyses. Furthermore, the analysis is also robust for missing data (Tabachnik and Fidell, [53]) and unequal sample sizes (more participating mothers than fathers). We will test interaction terms between parental sex (mother versus father) and intervention group (intervention versus control), to test whether the (possible) effect of the intervention is the same for both mothers and fathers. We will also calculate the between-group effect sizes at 6 (t3) and 10 weeks postpartum (t4). We will calculate Cohen’s *d* by subtracting the two mean scores and dividing them by the pooled standard deviations. A Cohen’s *d* of 0.2 can be assumed small, 0.5 to be moderate, and 0.8 to be large [13].

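### The primary outcome counts prenatal expectation scores at t0 and t1, although the objective is postpartum: model t3 and t4 as outcome, with t0 as baseline covariate

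*Protocol article*

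**What the plan says.** All references are to the protocol article.

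- **Assessments and outcomes, Primary outcome:** "The primary outcome is maternal parenting stress (assessed at t0; t1; t3; and t4". The same paragraph adds: "For the administration before birth (t0 and t1), the items were slightly rephrased to capture possible stress-raising expectations of parenthood".
- **Objectives:** "The primary objective of this study is to determine the postpartum effect of the intervention on maternal parenting stress".
- **Fig. 2 caption, order of events:** "participants are asked to sign an informed consent form and to complete the baseline questionnaire. Then, participants are randomized". So t0 comes before allocation.
- **Fig. 2 caption, start of intervention:** "The intervention starts with a home visit (at t1".
- **Intervention:** "Parents will receive access to the psycho-education materials (booklet and video) directly after randomisation". This is dated to weeks 26–34, with the home visit at weeks 34–36.
- **Abstract, Methods/design:** places an assessment "during the home visit (34–36 weeks of pregnancy". The section Assessments and outcomes says that everything except the infant diary is completed online.
- **Statistical analysis, Primary outcome:** one mixed multilevel model compares parenting stress between arms, with mothers and fathers nested in couples and a test of parental sex by group. No outcome occasions are named for the model. Between-group effect sizes are planned at t3 and t4: "We will calculate Cohen’s *d* by subtracting the two mean scores and dividing them by the pooled standard deviations".
- **Statistical analysis, Secondary outcomes:** the control variables are demographics, attachment style, and delivery and birth data. Baseline parenting stress is not among them.

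**The concern.** Two of the four occasions that define the primary outcome fall outside the stated objective. They also differ in content from the other two: before birth the questionnaire asks what a parent expects, and after birth what a parent experiences.

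Neither prenatal score is a postpartum outcome. The t0 score is taken before allocation and cannot show a treatment effect. The t1 score is taken after the intervention arm has received the booklet and video, so it is not a second baseline either.

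Because the model is not tied to t3 and t4, the plan does not fix which contrast answers the primary question. An analyst could choose a specification that dilutes the postpartum effect. Separately, the t0 score is a natural covariate for postpartum stress, and the plan does not give it that role.

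**Working it through.** **1. The plan's own figure.** Inputs from Sample size calculation: d = 0.50, power 80%, alpha 0.05 (taken as two-sided). The two-sample t-test needs 63.8, so 64 per arm and 128 in total, with power 80.1%. The stated size reproduces. It rests on a single comparison of two means.

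**2. Timing, from the sections side by side.**

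| Occasion | Relative to randomisation | Items | Can show a postpartum effect? |
|---|---|---|---|
| t0 (weeks 26–34) | before | expectation | no |
| t1 (weeks 34–36) | after; materials already released | expectation | no |
| t3 (6 weeks after birth) | after | experience | yes |
| t4 (10 weeks after birth) | after | experience | yes |

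The Fig. 2 caption and the Intervention section disagree on when the intervention starts. On either account, t1 is after randomisation.

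**3. Size of the dilution if all four occasions were averaged.** The effects by occasion are assumptions: 0 at t0, 0.50 at t3 and t4, and 0 to 0.25 at t1.

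- t1 effect 0: (0 + 0 + 0.50 + 0.50)/4 = 0.25
- t1 effect 0.25: (0 + 0.25 + 0.50 + 0.50)/4 = 0.3125

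With 64 mothers per arm and one common assumed correlation of 0.3 to 0.7 between occasions (normal approximation), power for that average is 54% to 36% in the first case and 73% to 52% in the second. If t1 already showed the full 0.50, the average would be 0.375 and power 87% to 67%.

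**4. Gain from using t0 as covariate.** With unit variance, the mean of t3 and t4 has variance factor (1 + r_post)/2. Adjusting for t0 makes it (1 + r_post)/2 − r_base². Power is that of a two-sample t-test at 0.50/√factor with 64 per arm. The correlations are assumptions, since the article gives none.

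| r_post (t3–t4) | r_base (t0–postnatal) | Factor | 0.50/√factor | Power |
|---|---|---|---|---|
| 0.6 | no covariate | 0.80 | 0.559 | 88.1% |
| 0.7 | no covariate | 0.85 | 0.542 | 86.1% |
| 0.6 | 0.3 | 0.71 | 0.593 | 91.5% |
| 0.7 | 0.3 | 0.76 | 0.574 | 89.6% |
| 0.6 | 0.5 | 0.55 | 0.674 | 96.6% |
| 0.7 | 0.5 | 0.60 | 0.645 | 95.2% |

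The covariate adds about 3 to 9 percentage points over averaging t3 and t4 alone. If expected and experienced stress correlate at only 0.1, the factors are 0.79 and 0.84, power is 88.5% and 86.5%, and the gain is under half a point.

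**The case against.** The best defence is that the list of four occasions is only a measurement schedule. The objective is postpartum and effect sizes are planned at t3 and t4 alone, so the intended target is fairly clear. A mixed model of repeated scores would normally carry group-by-time terms, and t0 then contributes information without being a covariate. Model detail is also what a condensed article commonly leaves to the full protocol or SAP.

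Much of this stands, and it rules out several stronger readings that a reader might infer:

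- **A four-occasion average is planned.** No section says so, and the dilution above applies only if it were done.
- **Change is measured from t1.** Only t0 is called baseline, and no change score from t1 is proposed.
- **Effect sizes use raw means only.** The text refers to two mean scores, which does not exclude model-estimated means.
- **The model has a couple-level random intercept and nothing below it.** The article names couple nesting but does not call it the only level. If it were, the inflated test would be parental sex by group, not the group contrast averaged over both parents.
- **The covariate lifts power from 80%.** That is the power of a single-occasion comparison. The fair comparator is t3 and t4 averaged without t0, at about 86–88%.

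The defence does not remove the mismatch in the text. The outcome definition includes two occasions that the objective excludes, the model sentence does not resolve this, and baseline parenting stress is absent from a control-variable list that is given.

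**Conclusion.** The point holds as a misalignment between outcome definition and objective, with a precision gain available at almost no cost. It is not evidence that a wrong analysis has been specified.

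The shrinkage from 0.50 to about 0.25–0.31 is conditional on an unstated averaging rule and an assumed t1 effect of 0 to 0.25. The rise from about 86–88% to 90–97% rests on assumed correlations. Because the prenatal items ask about expectations, the lower end is the safer guess, and a very weak correlation would leave almost no gain. The sample size of 128 is unaffected.

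The two descriptions of when the intervention starts, and of how t1 is collected, do contradict each other. They are minor: t1 is post-randomisation on any reading, so the recommendation does not depend on them.

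**What to change.** - In the primary model, use t3 and t4 as the only outcome occasions.
- Name one primary contrast for mothers, for example the adjusted group difference averaged over t3 and t4.
- Include the t0 parenting stress score as covariate. A longitudinal model with t0 means constrained equal across arms is an acceptable alternative.
- Report t1 separately as a post-randomisation prenatal measure, never as baseline.
- State that the model allows for repeated measures within parent as well as parents within couple.
- Take the t3 and t4 effect sizes and their intervals from the model.
- Reconcile the Fig. 2 caption with the Intervention section on when the intervention starts, and the Abstract with Assessments and outcomes on how t1 is collected in each arm.

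The cost is wording. Every score needed is already in the assessment schedule, and no participants or visits are added. Trial status reports recruitment ongoing, with nine of 59 participants through the protocol, so the change can be made before analysis.
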